### Supporting self-management of pain and analgesics’ side effects

Three recent meta-analyses focusing on the effects of psychosocial interventions to support cancer pain management from 1983 to 2012 found that, while gaining attention, the psychosocial approach to pain management remains understudied [24–26]. The two most common intervention types were skill training and education [25]. Regarding the main outcome measures, i.e., effects on pain intensity, pain interference in daily activities, knowledge, and attitudes towards cancer pain and analgesics, these meta-analyses revealed various significant, though moderate overall improvements. Further, a systematic evaluation of interventions’ content, structure, and efficacy to improve patients’ self-management of cancer pain revealed no discernible patterns with respect to components, duration, or delivery type or mode [27]. We found no studies that focused on the side effects of analgesics.

To date, little research has focused on interventions supporting FCs in patients’ cancer pain self-management. First, Keefe et al. [28] tested the feasibility of a partner-guided cancer pain management training program with 78 end-of-life patients and their FCs. Intervention group FCs showed significantly higher levels of self-efficacy regarding support for the control of pain and other symptoms. Second, in a randomized controlled trial (RCT) of caregiver assisted coping skill training for cancer patients and their FCs, Porter et al. [29] reported significant results compared with an education program. Additionally, enhanced knowledge of cancer pain management led to both decreased anxiety symptoms in both groups and increased symptom management self-efficacy in FCs. However, as this study lacked a standard care control condition, these results should be interpreted with caution. Third, Hendrix et al. [23] tested an individualized training intervention on self-efficacy in 120 patient-caregiver dyads. FCs in the intervention group demonstrated significant increases in self-efficacy regarding pain control, prevention of infections, maintenance of nutrition, and practical home care issues.

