### Random assignment

As shown in Fig. 2, patients and FCs who have provided written consent are stratified by site and randomized 1:1 either to a six-week intervention group (IG) or to a usual care group (CG). A permuted block procedure, with blocks of 2, 4 and 6, is used to create a computer generated randomization list. This procedure should ensure approximately equal distribution of patients per group and per centre. The Clinical Trial Unit (CTU) of one of the included university hospitals provides the list, which is accessible from all settings.

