### Quantitative data: variables and measurement

Table 2 provides an overview of the study variables and data collection points for patients and FCs.

**Table 2 Tab2:** Study variables and measurement timetable

Study variable	Instrument	Assessed in patients	Assessed in FCs	Week 0	Week 1	Week 2–5	Week 6
Demographics, patient	Patient Information Questionnaire	X		X			
Demographics, FC	FC Information Questionnaire		X	X			
Clinical data	Medical Record Review Form	X		X			
Average pain and worst pain	Pain management diary^a:^ Brief Pain Inventory (BPI)	X		X	X	X	X
Pain alleviation through pain medication		X		X	X	X	X
Pain interference with function		X		X	X	X	X
Duration of pain Bowel movements and use of laxatives Side-effects of pain and cancer treatment	Pain management diary^a:^	X		X	X	X	X
Knowledge of cancer pain	Patient Pain Questionnaire	X		X			X
	Family Pain Questionnaire		X	X			X
Constipation	Constipation Assessment Scale	X		X	X	X	X
Self-efficacy	Self-Efficacy Questionnaire in patients with cancer	X		X			X
	Caregiver version of the Self-Efficacy Questionnaire		X	X			X
Anxiety and depression	Hospital Anxiety and Depression Scale	X		X			X
Functional status	Eastern Cooperative Oncology Group Performance Status	X		X			X

Note. ^a^Pain management diary: daily assessment of average and worst pain, pain alleviation, and pain interference with function via *BPI* Brief pain inventory as well as duration of pain, bowel movements/ use of laxatives, side effects of pain and of cancer treatment via pain management diary

Questionnaires employed in this study are applied in their German versions, for which validity and reliability have been established. The primary patient outcomes are selected analgesics’ side effects (constipation, nausea, emesis, and concentration difficulties), self-efficacy, and knowledge of cancer pain management. Primary FC outcomes are self-efficacy and knowledge of cancer pain management. The secondary outcomes are patients’ average and worst-pain intensity. Anxiety, depression, functional status, and cancer-related symptoms are measured as covariates. Our analytical models will also control for age, education, time since diagnosis and current disease status.

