### Data analysis

Quantitative data will be compiled and analysed using SPSS 24.0. Data will be retrieved from the SecuTrial® database. Data will be systematically examined for out of range values and data inconsistencies. As appropriate, descriptive statistics will be calculated, including means and standard deviations for interval variables and frequencies, as well as percentages for categorical variables. An intent-to-treat analysis will be applied, using a significance level of .05 [55]. Although premature withdrawal is expected to be a random process, participants who completed the study will be compared with those who did not based on demographics, treatment group and other salient variables.

#### Data analysis for aim 1

Generalized linear mixed models will be applied to determine differences between the IG and the CG analgesic side effect developments throughout the intervention. This approach allows calculation of the main group and time effects, and of group-by-time interaction. The influence of missing data on the model results will be examined using sensitivity analysis [56]. Change scores for each patient as well as Cohen’s d will be calculated for each variable of interest.

#### Data analysis for aim 2

Our quantitative analysis will use descriptive statistics to summarize PPQ/FPQ items’ distribution characteristics. Generalized linear mixed models will be applied to determine differences between the IG’s and the CG’s knowledge of cancer pain management throughout the intervention. The influence of missing data on the model results will be examined using sensitivity analysis [46]. Change scores for each patient/FC as well as Cohen’s d will be calculated for each variable of interest.

For qualitative data analysis, transcript data will be stored and analysed in ATLAS.ti 7. Field notes and audiotapes of telephone calls, home visits and interviews will serve as qualitative data to explore both the IG’s and the CG’s the learning processes concerning knowledge of cancer pain and pain self-management. Data will be analysed via interpretive description–an approach using stepwise, systematic and iterative processing of data to arrive at a meaningful description and interpretation [57].

Information from quantitative and qualitative data collection will be combined within a mixed method matrix. Qualitative and quantitative results related to each German PPQ/FPQ item will be integrated in a final synthesis [39, 58].

#### Data analysis for aim 3

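### The named covariate set omits site, uses baseline outcome values less efficiently than it could, and does not tie anxiety, function and symptom covariates to week 0

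*Protocol article*

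**What the plan says.** Under *Quantitative data: variables and measurement*, the protocol article gives the covariates in two sentences: "Anxiety, depression, functional status, and cancer-related symptoms are measured as covariates. Our analytical models will also control for age, education, time since diagnosis", the second ending with current disease status. Neither sentence gives a time point, and neither mentions site or the baseline value of the outcome.

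Under *Random assignment*, participants are "stratified by site and randomized 1:1". There are three sites.

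Under *Data analysis for aim 1*, the side-effect outcomes are analysed with generalized linear mixed models, of which the article says: "This approach allows calculation of the main group and time effects, and of group-by-time interaction". Aim 2 uses the same class of model for knowledge. Both aims also plan change scores and Cohen's d. Site does not appear, and no one term is named as the efficacy test.

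Table 2 schedules the HADS and the ECOG-PS at weeks 0 and 6, the diary symptoms from week 0 through week 6, and the knowledge questionnaires at weeks 0 and 6 only.

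**The concern.** Three features of the stated model leave room for improvement.

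1. **Site.** Stratified allocation balances the arms within site. An analysis that ignores the stratification factor leaves between-site variation in the error term, so standard errors tend to be slightly too large.
2. **Baseline outcome.** With a free group effect at week 0, the group-by-time term for a two-visit outcome is a comparison of changes. It is unbiased, but it carries the full noise of the week-0 measurement.
3. **Covariate timing.** HADS, ECOG-PS and diary symptoms exist both before and after randomisation. In a repeated-measures model they could be entered as time-varying covariates. If the intervention shifts them, adjusting for later values removes part of its effect. Symptoms need the most care: the diary supplies nausea, emesis, constipation and concentration difficulties as primary outcomes, and the article names no separate instrument for cancer-related symptoms.

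At stake are some precision and, only if later covariate values were used, bias in the treatment effect.

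**Working it through.** **Step 1: the plan's own figure.** 136 evaluable patients and 35% attrition give 136/(1 − 0.35) = 209.2, rounded up to 210, as stated. No SD is given for the 136. Assuming a two-sided 5% test, 80% power and 68 per arm, d = (1.960 + 0.842) × √(2/68) = 0.480, so the implied SD is 0.99/0.480 = 2.06 NRS points. This concerns average pain, a secondary outcome in this sub-study. Every power figure below is therefore illustrative.

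**Step 2: what is listed and when it is measured.**

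| Variable | Named for adjustment? | Measured |
|---|---|---|
| Site | No (stratification factor) | At randomisation |
| Week-0 value of the outcome | No (can be a time point; used in change scores) | Week 0 |
| Anxiety, depression (HADS) | Yes, no time point | Weeks 0 and 6 |
| Functional status (ECOG-PS) | Yes, no time point | Weeks 0 and 6 |
| Cancer-related symptoms | Yes, no time point or instrument | Diary symptoms: weeks 0 to 6 |

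**Step 3: baseline handling, one pre and one post value.** Take complete data, equal variance at both visits and baseline correlation ρ. Relative to the variance of a post-only comparison, the change contrast has 2(1 − ρ) and baseline adjustment has 1 − ρ². The ratio is (1 − ρ²)/[2(1 − ρ)] = (1 + ρ)/2. The document gives no ρ, so a range is assumed.

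| ρ | Change | Adjusted | Ratio | Power, change | Power, adjusted |
|---|---|---|---|---|---|
| 0.3 | 1.40 | 0.91 | 0.65 | 65.8% | 83.6% |
| 0.5 | 1.00 | 0.75 | 0.75 | 80.0% | 89.9% |
| 0.7 | 0.60 | 0.51 | 0.85 | 95.1% | 97.5% |

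The power columns use difference 0.99, SD 2.06 and 68 per arm. The ratio applies to knowledge. For side effects measured weekly, it depends on the coding of time and the covariance structure, which the article does not give.

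**Step 4: site.** For a plain post-treatment comparison in which site explains a share s of outcome variance (assumed), the unadjusted test has type I error 2[1 − Φ(1.960/√(1 − s))]: 4.4% at s = 0.05 and 3.9% at s = 0.10. Power is Φ(0.842/√(1 − s)) without site and Φ(2.802/√(1 − s) − 1.960) with it: 80.6% against 82.0% at s = 0.05, and 81.3% against 84.0% at s = 0.10. In a group-by-time contrast, a constant site difference cancels from each patient's change (exactly with complete data and an identity link). So these losses of 1 to 3 points do not transfer to the planned model, where the loss should be smaller.

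**Step 5: covariate timing.** If the intervention shifts a later covariate by *a* SD and the within-arm slope of outcome on covariate is *b*, adjustment removes *a* × *b* SD. At week 0, *a* = 0 in expectation because of randomisation, so nothing is removed. For later values the document gives neither *a* nor *b*. Assuming *a* = 0.3 and *b* = 0.4, 0.12 SD goes, which is 0.12/0.48 = 25% of the pain effect in Step 1. With *a* from 0.2 to 0.5 and *b* from 0.3 to 0.5, the share runs from 0.06/0.48 (about 12%) to 0.25/0.48 (52%). These shares show the mechanism and do not estimate what would happen in this trial.

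**The case against.** The strongest reply is that a condensed article may leave covariate timing, a site term and baseline handling to the full plan, and that its list need not be exhaustive. This stands in part: the full plan may settle all three. But the article does state a model and name its covariates, and that stated set can be improved as it stands.

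Four stronger readings are tempting. The document supports none of them.

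- **That the plan adjusts for post-randomisation values.** It does not say so. Week-0 values exist for HADS, ECOG-PS and the diary symptoms, and a week-6 measurement may serve the parent study. Nor does the article show that anxiety mediates the effect. It reports of one earlier trial that "enhanced knowledge of cancer pain management led to both decreased anxiety symptoms in both groups", but that trial had no standard-care arm and the article itself urges caution. A fall in both arms is not a difference between arms. The overlap between symptom covariates and side-effect outcomes is plausible but is also an inference.
- **That the baseline outcome is ignored.** Week 0 is available to the repeated-measures model, and change scores use it. What remains is an efficiency point.
- **That the knowledge effect is halved.** A group main effect averaged over weeks 0 and 6 would be (0 + Δ)/2, but the article does not make that main effect its efficacy test. The group-by-time term is not halved.
- **That omitting site costs material power.** Step 4 shows why the loss is small and largely cancels in the planned contrast.

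**Conclusion.** The point holds as a modest improvement to a stated model, together with an ambiguity to close. The stratification factor is missing from the named adjustment set. The week-0 outcome is used validly but not efficiently: for knowledge, baseline adjustment would cut the variance by 15% to 35% (ratio 0.85 to 0.65), given ρ between 0.3 and 0.7, complete data and equal variances. The anxiety, depression, function and symptom covariates have no fixed time point. That matters only if values after week 0 were used, and the size of any resulting bias is unknown from the document. The primary outcomes' power cannot be computed because the sample size rests on pain.

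**What to change.** For each outcome, model the post-baseline values with arm, week, arm-by-week, the week-0 value of that outcome and site. Outcomes measured only at weeks 0 and 6 need no week terms. A mixed model with the arms constrained to be equal at week 0, plus site, is an alternative. Name the week-6 arm difference as the efficacy contrast. State that HADS, ECOG-PS and cancer-related symptoms enter only as week-0 values, and say which instrument supplies the symptoms.

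The cost is two degrees of freedom for three sites and a change of analysis wording. All the variables are already collected, so no new data are needed.

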#### Medical record review form

Clinical data from patients’ medical records include the date of the initial diagnosis, type of tumour, existence of any metastases (no/yes regarding localization of metastases), comorbidities, and completed or current tumour therapy.

#### Patient/FC information questionnaires

These questionnaires assess socio-demographic data including age, sex, living alone (yes/no), employment status and educational level.

#### Pain management diary

A pain management diary is used to assess analgesics’ side effects for each 7-day period. Patients are asked to rate 12 side effect items on an 11-point NRS (0–10: 0 = no symptom experience; 10 = strongest imaginable symptom experience). Our analysis will focus on constipation, nausea, emesis, and concentration difficulties. On a second 11-point NRS (0 = no pain; 10 = strongest imaginable pain) patients also rate their daily average and worst pain intensity.

#### Brief pain inventory

Pain intensity, i.e., average and worst pain, is measured on 0–10-point NRSs, which are part of the German version of the BPI. Daily pain scores will be averaged for each week of the study. The BPI is a pain measurement tool with reliability and validity established as excellent [44, 45].

#### Constipation assessment scale (CAS)

The CAS, an 8-item self-report tool, is completed weekly to measure the presence and severity of constipation (0 = no problem, 1 = some problem, 2 = severe problem). The total possible score ranges from 0 (no constipation) to 16 (severe constipation). A score of ≥2 will trigger the use of a constipation management plan. This scale’s validity and reliability have been established [46, 47].

#### PPQ and FPQ

The nine-item PPQ measures individuals’ knowledge of cancer pain. In cases of patient/FC dyads, a similar tool, the FPQ, is used for the FC [48]. Each item is scored using a 0–10-point NRS, with an overall/average score obtained by summing the items and dividing by 9. Extensive psychometric testing of the PPQ’s and the FPQ’s English versions has established excellent validity and reliability [49, 50]. As a part of their pilot study, Koller et al. [33] translated the English PPQ/FPQ into German.

#### Self-efficacy questionnaire in cancer patients and family caregivers

The Self-Efficacy Questionnaire includes 15 items measuring perceived ability to manage specific aspects of pain on a scale ranging from 10 (very uncertain) to 100 (very certain). The questionnaire is separated in three subscales: one for pain management, one for physical function and one for other symptoms. A total score is calculated by summing the scores for each of the subscales. To assess caregivers’ confidence regarding their ability to support cancer pain management, a caregiver version of the self-efficacy scale was used. This version is identical to that applied in cancer patients except that caregivers are asked to rate how confident they are that they can support the control of patients’ cancer pain [22]. Construct validity and reliability have been established for these questionnaires [51, 52].

#### Hospital anxiety and depression scale (HADS)

The HADS, a non-diagnostic self-report screening instrument, is used to assess anxiety and depression symptomatology. Based on two 7-item subscales, each using a 4-point (0–3) Likert-type scale, a score of 11 or more (of a possible 21) on either subscale indicates significant psychological morbidity (< 8 = clinically insignificant; 8–10 = borderline; 11–21 = indicate significant psychological morbidity) [53].

#### Eastern cooperative oncology group performance status (ECOG-PS)

The ECOG-PS measures functional status, i.e., the capacity to perform a variety of activities considered normal for most people. Developed in 1960, the scale has been widely used in clinical trials and oncology practice [54]. It consists of a single 5-point scale using verbal descriptors (0 = “fully active”, 4 = “completely disabled”).

### Qualitative data

#### Data from intervention sessions

All intervention sessions are audio recorded by the IN who provides the intervention. The PhD student (SV) then listens to these audio-recordings and transcribes all relevant passages, that is, all that concern side effect management, learning processes, or FC involvement. Additionally, field notes serve as qualitative data.

#### Individual post-RCT interviews

Selected patients and FCs are interviewed by specially trained nurses who are not yet involved in the study procedures. These nurses are experienced in conducting individual interviews and have been trained by the primary investigator and the study coordinator. Following an interview guide, they ask open-ended questions to explore patients’ and FCs’ experiences with pain management and related interactions with clinicians. To better understand the degree to which the intervention meets individual needs and to identify remaining difficulties regarding pain management, participants in the IG are also asked to discuss their perceptions of the study intervention’s burdens and benefits.

Focusing on PEINCA-FAM, we hope to identify remaining difficulties concerning side effect management, to explore patients’ and FCs’ learning processes during the intervention, and to explore the FCs’ involvement and self-efficacy. Interviews, which last approximately 60 min, are audio recorded and transcribed in standard German. So that relevant new topics can be integrated in the interview guide, analyses are performed in parallel with data collection.

### Data analysis

Quantitative data will be compiled and analysed using SPSS 24.0. Data will be retrieved from the SecuTrial® database. Data will be systematically examined for out of range values and data inconsistencies. As appropriate, descriptive statistics will be calculated, including means and standard deviations for interval variables and frequencies, as well as percentages for categorical variables. An intent-to-treat analysis will be applied, using a significance level of .05 [55]. Although premature withdrawal is expected to be a random process, participants who completed the study will be compared with those who did not based on demographics, treatment group and other salient variables.

#### Data analysis for aim 1

Generalized linear mixed models will be applied to determine differences between the IG and the CG analgesic side effect developments throughout the intervention. This approach allows calculation of the main group and time effects, and of group-by-time interaction. The influence of missing data on the model results will be examined using sensitivity analysis [56]. Change scores for each patient as well as Cohen’s d will be calculated for each variable of interest.

#### Data analysis for aim 2

Our quantitative analysis will use descriptive statistics to summarize PPQ/FPQ items’ distribution characteristics. Generalized linear mixed models will be applied to determine differences between the IG’s and the CG’s knowledge of cancer pain management throughout the intervention. The influence of missing data on the model results will be examined using sensitivity analysis [46]. Change scores for each patient/FC as well as Cohen’s d will be calculated for each variable of interest.

For qualitative data analysis, transcript data will be stored and analysed in ATLAS.ti 7. Field notes and audiotapes of telephone calls, home visits and interviews will serve as qualitative data to explore both the IG’s and the CG’s the learning processes concerning knowledge of cancer pain and pain self-management. Data will be analysed via interpretive description–an approach using stepwise, systematic and iterative processing of data to arrive at a meaningful description and interpretation [57].

Information from quantitative and qualitative data collection will be combined within a mixed method matrix. Qualitative and quantitative results related to each German PPQ/FPQ item will be integrated in a final synthesis [39, 58].

#### Data analysis for aim 3

For the quantitative analysis, to determine associations between FCs’ pre- and post-intervention score changes regarding self-efficacy, knowledge of cancer pain and patients’ average and worst-pain intensity between the two groups, we will calculate Pearson correlation coefficients.

Qualitative data will be generated in the same way as for aim 2 via field notes, recordings of telephone calls, home visits and interviews. Data will be analysed by applying interpretive description [57].

Information from quantitative and qualitative data collection will be combined within a mixed method matrix and integrated in a final synthesis [39, 58].

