### Aims

PEINCA-FAM aims to test the adapted German PRO-SELF © Plus PCP pain self-management intervention to reduce cancer outpatients’ analgesics’ side effects, to explore patients’ and FCs’ knowledge of cancer pain and their learning processes, and to investigate FCs involvement in patients’ pain self-management and associations between their self-efficacy, knowledge of cancer pain and patients’ pain intensity. Specific aims of this study are: (1) to test the efficacy of the adapted German PRO-SELF © Plus PCP to reduce analgesics’ side effects by focusing on constipation, nausea, emesis and concentration difficulties; (2) to test the efficacy of the adapted German PRO-SELF © Plus PCP to improve knowledge of cancer pain management in patients and FCs and to qualitatively explore patients’ and FCs’ learning process during the intervention; and (3) to explore the association between FCs’ self-efficacy and knowledge of cancer pain with patients’ pain intensity and to qualitatively explore FCs’ influence on patients’ pain self-management.

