### Sample size determination

The results of the above-mentioned pilot study (Koller et al. [33]) included a maximum mean alleviation of 0.99 NRS (0–10) for average pain and a mean alleviation of 1.27 NRS (0–10) for the worst pain compared to the control group in week nine. For these two endpoints, based on average pain improvement data, an alpha error of 0.05 (95%) and a beta error of 0.2 (80%) would require a 136-patient sample to achieve sufficient statistical power. Estimating an attrition rate of 35% over the 6-week study period, it will be necessary to recruit a total sample of 210 patients. We expect to recruit 50% of patients along with FCs. This number will be sufficient. Based on Wells, Hepworth, Murphy, Wujcik, and Johnson [40], who assessed initial effects of an intervention to increase knowledge and positive beliefs about cancer pain management in patients using the Family Pain Questionnaire (FPQ), an improvement in knowledge and beliefs were found [F (1,62) = 18.2, *p* < 0.001]. At an alpha error level of 0.05, a sample size of 32 FCs should be sufficient to achieve a statistical power of 80%.

With respect to the sample size for the qualitative part, a sample of 42–60 patients and FCs should supply sufficiently redundant data to discover patterns, commonalities and differences among the groups.

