## Discussion

This study is the first to evaluate the effects of a psychoeducational intervention to reduce analgesics’ side effects and to explore the involvement of FCs in pain management in a sample of Swiss cancer outpatients and their FCs. As with other chronic illnesses, cancer places new demands on patients and their FCs to manage their care; however, to do so effectively requires specialized skills. Therefore, to achieve adequate pain and side effect self-management, cancer patients and their FCs require educational interventions. Their self-management support should focus on enhancing patients’ and FCs’ pain management knowledge and self-efficacy, while improving their use of pain and side effect relief strategies [24, 59, 60].

This RCT involves the evaluation of a multicomponent self-management support intervention that combines monitoring of pain, side effects and medication based on nurse coaching via weekly in-home or telephone visits, skill building, and information provision. Compared to usual care, self-management support is expected to result in improved control of pain and analgesics’ side effects, as well as enhanced self-efficacy and knowledge [61].

Previous qualitative studies on home cancer pain management have showed that cancer patients have to manage diverse analgesics’ side effects, which is an ongoing multidimensional process [12, 32]. The complexity of this process means that, in addition to strategies and techniques for effective pain management, it is important to buttress both patients’ and FCs’ self-management and self-efficacy via an effective, holistic side effect management regimen [12, 62].

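### Aim 3 plans plain Pearson correlations with no term for randomised arm and does not say whether they are pooled or within arm; if pooled, the treatment effect alone induces a correlation

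*Protocol article*

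**What the plan says.** Aim 3 (Protocol article, Aims) is "to explore the association between FCs’ self-efficacy and knowledge of cancer pain with patients’ pain intensity", together with a qualitative part. It does not refer to treatment arm.

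The section Data analysis for aim 3 names one quantitative method. The FC side consists of the changes in the two FC scores, self-efficacy and knowledge, from before to after the intervention. For their relation to the patient side the sentence reads: "patients’ average and worst-pain intensity between the two groups, we will calculate Pearson correlation coefficients". No adjustment for arm, baseline or any other variable is attached to these coefficients.

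The model for aim 1 does handle arm: "This approach allows calculation of the main group and time effects, and of group-by-time interaction". The Discussion says of the intervention that "self-management support is expected to result in improved control of pain and analgesics’ side effects, as well as enhanced self-efficacy and knowledge".

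**The concern.** By the Discussion's own statement, randomised arm is an intended cause of both variables to be correlated: FC knowledge and self-efficacy should rise, and patient pain should fall. If dyads from both arms enter one Pearson coefficient, the gap between the arm means adds a negative component to r. That component is there even if, within each arm, dyads whose FC learns more do no better on pain than other dyads.

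A significant pooled r could then be reported as evidence that FC knowledge or self-efficacy goes with lower patient pain, when it may only restate that the intervention moved both. The Background says that such correlations have not been investigated before, so the result is likely to be read as first evidence.

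The sentence is also open to two readings, pooled or per arm. They answer different questions, and nothing in the article prevents the choice from being made after the data are seen.

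**Working it through.** **The plan's own figures** (Sample size determination)

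- Recruited patients: 136/(1 - 0.35) = 209.2, rounded up to 210. This reproduces the stated total.
- FCs: 32 are said to be enough for 80% power. With the knowledge effect below, a two-sided 5% t-test needs 15 per arm (30 in total), and 16 per arm gives 84% power. The 32 is sufficient on that assumption.

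Aim 3 has no sample size figure of its own.

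**Inputs for the check**

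- Dyads: half of the patients are expected to bring an FC, so 210 × 0.5 = 105. If the 35% attrition also applies to dyads (assumption), 105 × 0.65 = 68.25, about 68, or 34 per arm under 1:1 allocation.
- Knowledge effect: the cited F(1,62) = 18.2 gives d1 = 2 × √(18.2/62) = 1.08, if it compares two groups of equal size (assumption).
- Pain effect: the article gives "a maximum mean alleviation of 0.99 NRS (0–10) for average pain and a mean alleviation of 1.27 NRS (0–10) for the worst pain" but no SD. Back-solving from 68 patients per arm at two-sided 0.05 (sidedness assumed) and 80% power: d2 = (1.960 + 0.842) × √(2/68) = 0.48. The implied SD is 0.99/0.48 = 2.06. With the same SD assumed for worst pain, d2 = 1.27/2.06 = 0.62.
- Self-efficacy effect: no figure is given.

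**Correlation induced by arm alone**

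Take 1:1 allocation, within-arm SD of 1 for both variables and zero within-arm correlation. The pooled covariance is -d1·d2/4 and the pooled variances are 1 + d1²/4 and 1 + d2²/4. Hence

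r = -d1·d2 / √[(d1² + 4)(d2² + 4)]

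- Average pain: -(1.08 × 0.48)/√(5.17 × 4.23) = -0.11
- Worst pain: -(1.08 × 0.62)/√(5.17 × 4.38) = -0.14

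**Rejection rate of the two-sided 5% test of r = 0** (20,000 simulated trials per setting, true within-arm correlation zero)

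| Knowledge d | Pain d | Induced r | 32 dyads | 68 dyads | 105 dyads |
|---|---|---|---|---|---|
| 1.08 | 0.48 | -0.11 | 9% | 15% | 21% |
| 1.08 | 0.62 | -0.14 | 12% | 21% | 31% |
| 0.5 | 0.48 | -0.06 | 6% | 8% | 9% |
| 0.5 | 0.62 | -0.07 | 7% | 9% | 11% |
| 0.3 | 0.3 | -0.02 | 5% | 5.5% | 5% |

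After removing the arm means (partial correlation given group), the rejection rate lay between 4.6% and 5.4% in every setting.

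**If the coefficients are calculated per arm**

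The induced correlation is zero, but precision suffers. By Fisher's z, 80% power with 34 dyads requires z = 2.80/√(34 - 3) = 0.503, that is r of about 0.46. A partial correlation given arm uses all 68 dyads: z = 2.80/√(68 - 1 - 3) = 0.350, that is r of about 0.34. Comparing the two arms' coefficients would need a difference in z of 2.80 × √(2/31) = 0.71.

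**The case against.** A reader might infer that the plan pools the arms. The article does not say so. The reference to the two groups at the end of the sentence can equally mean one coefficient per group, then compared, and on that reading there is no bias. This objection stands, and the point is therefore that the sentence leaves the reading open.

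The size rests on assumptions. The article gives no standardised effect for knowledge, no SD for pain and no effect for self-efficacy, and it does not say that dyads drop out at the patients' rate. Nor is it clear whether pain enters as a change or as a level. This also stands. Much higher error rates can be produced, for instance about 31% at 68 dyads with a pain effect of 0.8 SD, but nothing in the article supports an effect that large. On the figures nearest to the article the induced r is modest, about 1% to 2% of variance (0.11² = 0.012; 0.14² = 0.020).

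Aim 3 is exploratory, and its quantitative sentence states no hypothesis or decision rule; only the general .05 level applies. Its qualitative half is untouched, so it would go too far to say that the aim would be left unanswered. But exploratory status relaxes error control. It does not make a pooled coefficient measure the within-arm association.

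A reader might also see a conflict with "Our analytical models will also control for age, education, time since diagnosis and current disease status". That sentence concerns models, and a descriptive correlation is not clearly one of them, so no contradiction is shown. Regression to the mean and floor effects are likewise not shown to create a correlation here: the scores come from different people on different instruments.

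Finally, a condensed article may leave detail to the full protocol or analysis plan. Here, however, the article does name the method, and as worded it admits a reading that does not fit the aim.

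**Conclusion.** The point holds in a limited form. The article names an unadjusted Pearson coefficient for two variables that the intervention is meant to move and does not fix whether it is pooled or within arm.

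If it is pooled, and there is no association within arms, r is about -0.11 to -0.14 and the nominal 5% test rejects in about 15% to 21% of trials at 68 dyads. This rests on a knowledge effect of 1.08 SD, a pain effect of 0.48 to 0.62 SD and equal SDs in both arms. With smaller effects the excess shrinks and nearly vanishes at 0.3 SD for both. The mechanism applies to pain as a change or as a week-6 level, since arm can affect either. If the coefficients are per arm, there is no bias, only the loss of precision from about 34 dyads in each.

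Aims 1 and 2 are not affected. The change is worth making because it removes the bias of one reading, avoids the loss of precision of the other and needs no new data.

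**What to change.** In Data analysis for aim 3, replace the plain Pearson coefficient with one of these, chosen before the data are analysed:

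- the partial correlation of FC score change with patient pain, given randomised group; or
- a linear model of patient pain on FC score change with randomised group as a term, where pain is either the change from baseline or the week-6 value adjusted for baseline pain.

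State which form of the pain variable is used. Report the arm-adjusted estimate with its 95% CI, separately for average and worst pain, and give the coefficient in each arm as description only.

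The cost is one degree of freedom for group, a second if baseline pain is added, and slightly more analysis work. The full list of covariates is not needed and would be heavy for about 68 dyads.
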